### Contamination

In departments with more than one nurse, nurses who counsel participants in the intervention group will not counsel participants in the control group, and vice versa. Nurses who counsel participants in the intervention group are asked not to discuss the content of the intervention with nurses who counsel participants in the control group. In departments with only one nurse, this separation is not possible. However, since all nurses in the intervention group will need to extend their meeting for the intervention, and since they all need to fill out a form during each meeting, contamination between groups will be diminished. It is unlikely that employees of the same company will participate in the study; therefore, it is unlikely that participants in the control group will receive detailed information about the content of the intervention. It is possible that participants in the intervention group will discuss the content of the intervention with those in the control group at the hospital in the waiting room or during chemotherapy treatment. However, we do not consider this possibility a serious risk of contamination.

Participants will be able to use any co-intervention they wish. Since it is likely that other vocational rehabilitation programs will have a significant effect on return-to-work, these co-interventions will be monitored by asking the participants at the end of the intervention if they have participated in any other vocational rehabilitation programs. Because the effect of other rehabilitation programs on return-to-work is unknown, these co-interventions will not be assessed.

### Usual care in the Netherlands

Employees who are diagnosed with cancer should be guided according to the blueprint of evidence-based guidelines of the Dutch Association of Occupational Physicians (NVAB) [30]. Furthermore, sick leave is covered in the Netherlands by the Improved Gatekeepers Act, which is in force during the first 2 years of sick leave. The act states that a sick-listed employee cannot be discharged and receives at least 70% of his/her wage. After 2 years of sickness, the sick-listed employee will be assessed for disability pension. The Improved Gatekeepers Act states that employers and sick-listed employees are responsible for work resumption, which means that both parties can be sanctioned. Furthermore, all sick-listed employees should have an occupational physician who should legally advise them about return-to-work.

### Training nurses to carry out the intervention

The nurses who carry out the intervention will participate in a half-day training course. This training course consists of education about the rights and obligations of sick-listed employees according to the Improved Gatekeepers Act and education about the return-to-work problems of cancer patients. For instance, education about the return-to-work rates of cancer patients, factors that can have an impact on the return-to-work outcomes (e.g. diagnosis, type of treatment, and work ability), and the role of colleagues, supervisors, and occupational physicians. Furthermore, extensive practice is given at each meeting by means of role-playing and discussions between trainer and trainees. The training course will be given by a trained psychologist and a researcher. For evaluation, all nurses are asked to give their opinions of the training course by filling out an anonymous questionnaire at the end of the course.

### Outcomes

The primary outcome parameters are return-to-work and quality of life. The secondary outcome parameters are work ability, work limitations, study feasibility, and direct/indirect costs of the intervention. The primary and secondary outcomes will be assessed at baseline and at 6, 12, 18, and 24 months after baseline. Participants will fill out the baseline questionnaires directly after signing the informed consent forms. The other questionnaires will be mailed with an enclosed free return envelope. It will take participants approximately 30 minutes to complete each questionnaire. The questionnaire has been pilot-tested with healthy subjects and cancer patients.

#### Effect evaluation

The study's effectiveness will be determined on the basis of the primary outcomes of return-to-work and quality of life and the secondary outcomes of work ability and work limitations, assessed at the long-term follow-up at 12 months and at the very long-term follow-up at 24 months. Prognostic factors will be taken into account in the effect analysis only if there are imbalances between the intervention group and the control group. Effectiveness will be inferred if participants in the intervention group will have a significantly shorter time to return-to-work than participants in the control group and if at the same time their quality of life does not significantly deteriorate. Return-to-work is measured both as the number of calendar days between the first day of sick leave and the first day at work (either part-time or full-time) sustained for at least 4 weeks and as the rate of return-to-work at follow-up. The first day of sick leave, the number of calendar days until return-to-work, and the return-to-work rates will be based on patient self-reporting on questionnaires [23]. Quality of life will be assessed with the SF-36 [31]. All subscales of the SF-36 will be taken into account (physical functioning, role limitations due to physical health problems, bodily pain, general health perceptions, vitality, social functioning, role limitations due to emotional problems, and general mental health). The SF-36 has been validated in a sample of cancer patients, and normative values have been determined [31]. Work ability will be assessed with the first 3 questions of the Work Ability Index (WAI) [32]. These questions concerns the evaluation of current work ability compared to their life time best and current physical and mental work ability with respect to their job demands. Acceptable measures for reliability and validity have been determined [33,34]. Work limitations will be assessed on the basis of the Work Limitation Questionnaire, where work limitations are defined as being inversely related to productivity [35]. This questionnaire consists of four different subscales: work scheduling, physical demands, mental demands/social demands, and output demands. The English version of the Work Limitation Questionnaire has been proven valid and reliable in populations of several chronic diseases [35] and cancer survivors [10,11,36]. The validity and reliability assessments of the Dutch translation of the Work Limitation Questionnaire are currently underway for healthy controls and cancer patients.

#### Process evaluation

Process evaluation is divided into the following parameters: 1) feasibility of the procedure, 2) satisfaction with the intervention, 3) participant compliance with the intervention, 4) nurse adherence to the protocol, and 5) evaluation of usual care. First, feasibility of the procedure will be assessed by a researcher on the basis of a checklist at the end of the study. Second, nurse and participant satisfaction with the intervention will be assessed by a questionnaire. Third, patient compliance with the intervention will be assessed by a questionnaire. Fourth, nurse adherence to the protocol will be assessed by a researcher on the basis of reports from the nurse. Fifth, evaluation of usual care will be assessed on the basis of a questionnaire and includes organisational factors such as received support from the organisation and the occupational physician.

#### Economic evaluation

For the economic evaluation, the work-related costs to society, the individual cancer patient, and the employer will be taken into account, since everyone incurs costs when an individual cancer patient does not return-to-work [37]. In this way, the costs and benefits will be calculated independently of those who bear these costs and those who receive the benefits. For the intervention group, direct costs such as the costs to carry out the intervention, and indirect costs, such as absenteeism or work productivity, lost earnings, and work adjustments will be taken into account. For the control group direct costs such as the costs to carry out care as usual, and indirect costs, such as absenteeism or work productivity, lost earnings, and work adjustments will be taken into account. The direct costs will be determined by means of the average nurse wage and the amount of time spent on each participant. The nurse will record the duration of each meeting at its completion. Indirect costs will be obtained by a questionnaire. Absenteeism will be determined by means of days on sick leave and on income and work productivity by the Work Limitation Questionnaire and on income [35]. Furthermore, lost earnings will be determined on the basis of the differences between income at baseline and income at follow-up. Work adjustments will be assessed by means of the cost of each work adjustment.

#### Prognostic and descriptive factors

We have taken into account as prognostic factors, all factors that were significant related to time to return-to-work in a prospective cohort study on the impact of cancer-and work-related factors on the return-to-work of cancer patients [17,18]. Prognostic factors will be assessed by questionnaires at all time points except for diagnosis and treatment, which will be retrieved from patient files. The prognostic factors include age, gender, education, diagnosis, cancer treatment, number of working hours according to contract, physical workload as measured by the Questionnaire Perception and Judgement of Work (VBBA) [38], importance of work as measured by a Visual Analogue Scale (VAS-scale), fatigue as measured by the Multidimensional Fatigue Inventory (MFI) [39], depression as measured by the Centre for Epidemiologic Studies for Depression Scale (CES-D) [40], co-morbidity, income, self-efficacy as measured by the general self-efficacy scale (ALCOS) [41], and global quality of life as measured on a VAS-scale. The descriptive factors include the number of days between the first day of sick leave and inclusion in the study, marital status, ethnicity [42], time since diagnosis, breadwinner status, position at work, shift work, years in current position, years of paid employment, and company size. These descriptive factors will be measured only at baseline.

### Statistical analysis

#### Effectiveness

All analyses, which will be performed to distinguish differences between the control group and intervention group, will be performed according to the intention-to-treat principle. All baseline data and data regarding primary and secondary outcomes will be presented using descriptive statistics. The number of days until participants' return-to-work will be analysed using the Kaplan-Meier survival method, and differences between groups will be tested with a log rank test. If necessary, the differences between the control group and the intervention group will be adjusted with a Cox regression analysis for confounders such as diagnosis and for the prognostic parameters. Longitudinal multilevel analysis will be used to examine differences between the control group and the intervention group with regard to improvement of the primary outcome of quality of life and the secondary outcomes of work ability and work limitations.

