### Participants

Patients are eligible to participate when they have a primary diagnosis of cancer, will be treated with curative intent, are employed at the time of diagnosis, are sick-listed, and are between 18 and 60 years old. Treatment with curative intent was defined as a 1 year survival rate of approximately 80%. The exclusion criteria are: 1) patients who are not able to speak, read or write Dutch sufficiently well, 2) patients who have a severe mental disorder or other severe co-morbidity, 3) Primary diagnosis of cancer has been made more than two months ago, 4) patients who will receive primary treatment at another hospital, and 4) patients who have a primary diagnosis of testicular cancer, non-melanoma skin cancer or melanoma skin cancer. This last exclusion criterion has been selected because, on average, these cancer patients do not experience significant problems with return-to-work; therefore, the intervention would not be useful for the majority of this patient group [5,25].

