### Sample size

The calculation of sample size is based on two earlier studies regarding return-to-work in cancer patients. Based on the study by Spelten et al. [18] with consecutive cancer patients, the expectation is that 18 months after diagnosis 36% of patients will not have returned to work [18] after care as usual in the control group. With regard to the intervention group, the expectation is that 19% of the patients will not have returned to work 18 months after diagnosis [23], based on the study by Nieuwenhuijsen et al. [23]. Due to the inclusion and exclusion criteria, a percentage of patients with relatively less severe return-to-work problems will not be included in this study and this may lead to less favourable return-to-work rates. However, our intervention is more comprehensive than in the study by Nieuwenhuijsen et al. [23] and thus the expectation is that the percentages of patients that will not have returned to work will be the same as in the study by Nieuwenhuijsen et al. [23]. This indicates an Odds Ratio of 0.41 of the intervention versus usual care for higher percentages of patients that are not returned to work, which is the same as an Odds Ratio of 2.4 of the intervention versus care as usual for higher return-to-work rates. Since, the incidence of outcome is more than 10%, the Odds Ratio overestimates the magnitude of the association and therefore, we calculated the Relative Risk based on the Odds Ratio [27]. This indicates a Relative Risk of not returning to work of 0.53 of the intervention versus usual care. Based on the PS Power and Sample size Program, with a power of 80% and two-sided significance level of p < 0.05, the sample size should be 109 patients in every arm, for a total of 216 patients [28]. Assuming that 20% of the initial patients will be lost to follow-up during the course of the study, 270 patients must be recruited to gather 246 patients at 24 months. To account for at least 10% missing data at baseline, 300 patients are intended to be included. Furthermore, a sample size of 300 will have sufficient power to be able to control for the prognostic factors in a Cox regression analysis since we assume that 5 to 10 variables will be included in the final model [17,18] and a sample size of 10 per included factor in a Cox regression analysis is considered sufficient [29].

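### Time to return-to-work is analysed by Kaplan-Meier with no place for death, in a cohort defined by about 80% one-year survival, so the proportions returned can be overstated in each arm

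*Protocol article*

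**What the plan says.** Four parts of the protocol article bear on this.

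- **Participants:** "Treatment with curative intent was defined as a 1 year survival rate of approximately 80" per cent. The text does not say whether this is a minimum for entry or the expected average, and gives no expected mortality for the cohort.
- **Effect evaluation:** return-to-work is measured in two ways, as calendar days from the start of sick leave to sustained work and as a rate at follow-up. Death is not mentioned for either.
- **Effectiveness (statistical analysis):** the number of days "will be analysed using the Kaplan-Meier survival method, and differences between groups will be tested with a log rank test", with Cox adjustment if needed. Death is not mentioned here either.
- **Sample size:** "36% of patients will not have returned to work" in the control group at 18 months, and "19% of the patients will not have returned to work 18 months after diagnosis" in the intervention group, "with a power of 80% and two-sided significance level of p < 0.05". Then "Assuming that 20% of the initial patients will be lost to follow-up during the course of the study", and finally "To account for at least 10% missing data at baseline, 300 patients are intended to be included". Death does not appear in this section, so it is unclear whether the 20% includes it.

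**The concern.** Death before return-to-work is a competing event: it removes the chance of returning. A standard Kaplan-Meier analysis censors it, which treats the dead as if they would later have returned at the same rate as the survivors. The log-rank comparison of return hazards among those alive remains valid, but one minus Kaplan-Meier is then not the proportion of patients who returned. With one-year survival of about 80% in the eligibility definition, the gap may not be negligible.

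At stake are the return-to-work proportions reported for each arm, which readers would use to judge how many patients get back to work. There is also a planning question. The comparison that sized the trial is of two rates at 18 months, and its power depends on how deaths enter those rates and on whether the 20% allowance is meant to absorb them.

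**Working it through.** **1. The plan's own figures.** Two proportions, 0.36 and 0.19, two-sided 5%, 80% power, pooled variance, no continuity correction: 108 per arm, 216 in total. The article gives 109 per arm and a total of 216. Inflation: 216/0.8 = 270 and 270/0.9 = 300. The stated chain therefore reproduces with 216 as the number remaining. The article also says "270 patients must be recruited to gather 246 patients at 24 months". That does not match a 20% loss (270 × 0.8 = 216), so 216 is used below.

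**2. Assumptions.** Constant hazards; deaths independent of return-to-work and equally frequent in both arms; 36% and 19% read as death-free rates at 18 months. One-year survival S is varied over 80%, 90% and 95%, because the article gives no cohort mean.

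- Return hazard, control: −ln(0.36)/18 = 0.0568 per month
- Return hazard, intervention: −ln(0.19)/18 = 0.0923 per month (hazard ratio 1.63)
- Death hazard: m = −ln(S)/12, which is 0.0186 per month at S = 80%

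**3. Proportion returned.** With deaths censored, 1−KM = 1 − exp(−λt). The actual proportion is the cumulative incidence, CIF = λ/(λ+m) × [1 − exp(−(λ+m)t)].

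Worked example, control, S = 80%, t = 24: 1−KM = 1 − exp(−0.0568 × 24) = 74.4%. CIF = (0.0568/0.0754) × [1 − exp(−0.0754 × 24)] = 63.0%.

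At 24 months:

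| One-year survival | Control, 1−KM / CIF | Intervention, 1−KM / CIF | Overstatement (points) |
|---|---|---|---|
| 80% | 74.4% / 63.0% | 89.1% / 77.4% | 11.4 and 11.7 |
| 90% | 74.4% / 68.6% | 89.1% / 83.2% | 5.8 and 5.9 |
| 95% | 74.4% / 71.5% | 89.1% / 86.2% | 2.9 and 2.9 |

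**4. Difference between arms.** At 24 months and S = 80%: 89.1 − 74.4 = 14.7 points by Kaplan-Meier and 77.4 − 63.0 = 14.4 points by cumulative incidence. The error nearly cancels.

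**5. Log-rank power.** Schoenfeld's formula, N = 270, S = 80%, death the only loss. Expected events are 135 × (0.559 + 0.719) = 173 by 18 months and 135 × (0.630 + 0.774) = 190 by 24 months. Power = Φ[√(events/4) × ln(1.63) − 1.96], which is about 89% and 92%.

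**6. The 20% allowance.** The allowance on 270 is 270 − 216 = 54. Deaths of 270 within 12 months are 54 at S = 80%, 27 at 90% and about 14 at 95%. With a constant hazard, deaths by 24 months (1 − S²) reach 20% once S is about 89% or lower, since √0.8 = 0.894.

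**7. Power of the 18-month rate comparison.** Deaths before return count as not returned, and 216 are analysed (108 per arm) after 20% other loss. The proportion not returned is 1 − CIF at 18 months.

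| One-year survival | Not returned, control / intervention | Power |
|---|---|---|
| No deaths (plan) | 36% / 19% | 80% |
| 95% | 38.0% / 21.2% | 77% |
| 90% | 40.0% / 23.5% | 74% |
| 80% | 44.1% / 28.1% | 69% |

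**The case against.** The strongest reply is that this is silence rather than error. The article states no censoring rule, and a condensed article may leave that rule to the full protocol or analysis plan. If deaths were kept at risk to the end of follow-up, one minus Kaplan-Meier would equal the cumulative incidence in the absence of other censoring. Nor does the article say that the follow-up rates are read from the Kaplan-Meier curve; it attaches Kaplan-Meier only to the number of days. The planning rates of 36% and 19% may already count deaths as not returned. This stands as a limit on the size of the point, which is conditional on the usual censoring and on those rates being death-free. It does not remove the point: the article names the estimator, and the usual use of that estimator does not give the proportion returned in a cohort with appreciable mortality.

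The second reply is that the trial's conclusion is untouched. Effectiveness is inferred from a significantly shorter time to return, without deterioration in quality of life. The log-rank test with deaths censored is a valid test of the cause-specific hazard and remains well powered. This stands in full.

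A reader might also infer that mortality takes the trial below its stated 80% power by deleting every death: 270 × 0.8^1.5 = 193 alive at 18 months (76%) and 270 × 0.8² = 173 at 24 months (71%). The documents do not support that. A patient who returned and later died already has the event. Under the same model 36% have died by 24 months, but only about 21% (control) and 16% (intervention) died before returning. The 71% also applies 18-month rates to a 24-month headcount.

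**Conclusion.** The point holds for the proportions returned in each arm. If deaths are censored, Kaplan-Meier overstates them at 24 months by about 11 to 12 points at 80% one-year survival, 6 at 90% and 3 at 95%, under constant hazards, independent deaths and death-free planning rates. Cumulative incidence is the better estimator here.

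Three stronger readings do not hold:

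- **The primary test is invalid or underpowered.** It is a valid cause-specific test, with power of about 89% to 92% at N = 270 if death is the only loss.
- **The cost-effectiveness ratio is badly biased.** Its denominator is the difference in rates between arms, which moves only from 14.7 to 14.4 points.
- **One year of deaths uses up the 20% allowance.** That is true only if the cohort's mean one-year survival is near 80%, which the Participants section does not state. At 90% or 95%, one-year deaths take half or a quarter of it.

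What remains on planning is narrower. The article does not say whether the 20% includes deaths. If deaths count as not returned and the 20% covers other loss only, power for the 18-month rate comparison falls to between 69% and 77% over the survival range examined, provided the 36% and 19% exclude death.

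**What to change.** 1. Estimate and plot return-to-work in each arm with the Aalen-Johansen cumulative incidence function, with death as a competing event.
2. Keep the log-rank test and describe it as the test of the cause-specific hazard of return.
3. In the return-to-work rates at follow-up, count patients who died before returning as not returned rather than dropping them. Apply the same rule in the cost-effectiveness ratio.
4. In the Sample size section, state the expected mortality and whether the 20% loss includes deaths. Say whether the 36% and 19% already count deaths, and give the power of the 18-month rate comparison over a range of mortality.

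The cost is small: some wording, a little code, and vital status with date of death sought in the patient files that the plan already uses for diagnosis and treatment. No new visits or questionnaires are needed. The reported rates and the power of the rate comparison will look slightly less favourable.

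### Quality of life is compared as improvement, with no baseline SF-36 adjustment named and covariates admitted only on imbalance; if this means an unconstrained change contrast, precision is lost for nothing

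*Protocol article*

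**What the plan says.** The Outcomes section of the protocol article states: "The primary outcome parameters are return-to-work and quality of life". On timing it says: "The primary and secondary outcomes will be assessed at baseline and at 6, 12, 18, and 24 months after baseline". Under Recruitment of study population, the baseline questionnaire is completed before the patient is randomised. Each SF-36 subscale therefore has a pre-randomisation value on the same scale.

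The analysis of quality of life is given in one sentence under Statistical analysis, Effectiveness: "Longitudinal multilevel analysis will be used to examine differences between the control group and the intervention group with regard to improvement of the primary outcome". The same sentence covers work ability and work limitations. It lists no fixed effects and gives the baseline score no role.

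The only covariate rule for this comparison is under Effect evaluation: "Prognostic factors will be taken into account in the effect analysis only if there are imbalances between the intervention group and the control group". The list under Prognostic and descriptive factors was drawn from factors related to time to return-to-work. It includes "global quality of life as measured on a VAS-scale" but none of the SF-36 subscales.

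Quality of life also enters the effectiveness decision. Besides faster return-to-work, effectiveness is inferred only "if at the same time their quality of life does not significantly deteriorate".

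**The concern.** *Improvement* most naturally means change from baseline. In a longitudinal model that is the group-by-time contrast with baseline as one of the outcome waves and the arm means left free at baseline. This contrast subtracts the whole of any baseline difference between the arms, rather than the share that carries over to follow-up. The lower the correlation between baseline and follow-up, the more precision is wasted.

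The imbalance rule does not repair this. It makes adjustment depend on the observed data, and even when triggered it draws on a list without the baseline value of the scale being analysed.

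At stake is the precision of a primary outcome. A noisier estimate makes a real benefit harder to show. If the deterioration condition is judged on this between-group contrast, a noisier estimate also makes real harm harder to show. That condition is met when nothing significant is found, so lost precision makes it easier to pass.

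**Working it through.** **The article's own figure.** The Sample size section rests on return-to-work only: "the expectation is that 18 months after diagnosis 36% of patients will not have returned to work" in the control group, and "the expectation is that 19% of the patients will not have returned to work 18 months after diagnosis" in the intervention group. With pooled variance, two-sided 5% and 80% power:

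n per arm = [1.96 × √(2 × 0.275 × 0.725) + 0.8416 × √(0.36 × 0.64 + 0.19 × 0.81)]² / 0.17² = (1.238 + 0.522)² / 0.0289 ≈ 107.1, so 108.

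This gives 216 in total, the article's total (its per-arm figure is 109). Then 216/0.8 = 270 and 270/0.9 = 300, also as stated. None of this concerns quality of life: the article gives no SD, effect size or correlation for it. I borrow 108 per arm as the number analysed.

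**Assumptions.** One follow-up visit, equal SDs (set to 1) at baseline and follow-up, and baseline-to-follow-up correlation rho = 0.5 with range 0.3 to 0.7.

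**Variances, in SD² per patient.**
- Change score: 2(1 - rho)
- Baseline-adjusted: 1 - rho²
- Cut from adjusting, as a share of the change-score variance: 1 - (1 + rho)/2 = (1 - rho)/2
- Ratio of change-score to adjusted variance: 2/(1 + rho)

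| rho | Change | Adjusted | Cut | Ratio | Power if adjusted, when change has 80% | Power on change, when adjusted has 80% |
|---|---|---|---|---|---|---|
| 0.3 | 1.40 | 0.91 | 35% | 1.54 | 94% | 62% |
| 0.5 | 1.00 | 0.75 | 25% | 1.33 | 90% | 68% |
| 0.7 | 0.60 | 0.51 | 15% | 1.18 | 86% | 73% |

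The two ways of stating the loss should not be mixed. Adjusting removes 15 to 35% of the change-score variance, which is the same as saying that the change contrast needs 1.18 to 1.54 times as many patients.

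**Check with all five visits.** I computed generalised least-squares variances for the last-visit contrast, with 108 per arm and equal correlations between visits. At rho 0.5 the unconstrained group-by-time contrast has variance 0.0185, exactly the change-score value 1.00 × 2/108. With arm means constrained equal at baseline it is 0.0139, exactly the adjusted value 0.75 × 2/108. The ratios at rho 0.3 and 0.7 also match the table. So a multilevel model is not inefficient in itself; the loss comes from leaving the baseline means free.

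**Shift given a chance imbalance.** If the arms differ by D at baseline, the change estimate moves by -(1 - rho)D. The standard error of D is √(2/108) = 0.136 SD, so a two-standard-error imbalance is 0.272 SD. The shift is then 0.7 × 0.272 = 0.19 SD at rho 0.3, 0.14 SD at rho 0.5 and 0.08 SD at rho 0.7, in favour of the arm that starts lower.

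**The other reading.** If only follow-up scores are compared, with no baseline term, the variance is 1 and adjusting cuts it by rho²: 9%, 25% and 49% at rho 0.3, 0.5 and 0.7. That reading does not avoid a loss either.

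**The case against.** The strongest objection is that the article never says baseline is ignored. A longitudinal multilevel analysis of improvement can hold baseline as a covariate, or as an outcome wave with equal arm means, and then the loss is zero. Model terms are commonly left to the full protocol or analysis plan, which is not shown. This stands: a reader might infer that the analysis fails to condition on baseline, but the text supports only that it points to a change contrast and names no adjustment.

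A reader might also infer a biased estimate. Under randomisation the change contrast is unbiased on average. The shift above is conditional on the realised imbalance, and one of two standard errors or more occurs in either direction in only about 5% of trials per subscale.

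Nor should the imbalance rule be read as forbidding a baseline SF-36 term. It governs listed prognostic factors, and that list was built for return-to-work. The absence of the SF-36 subscales from it is silence, not a prohibition.

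The size of the loss rests on an assumed correlation and a borrowed sample size. This also stands.

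Finally, a mandatory baseline covariate would drop patients without a baseline score. The Sample size section allows for at least 10% missing data at baseline, and the analysis is meant to be by intention to treat. This is a fair objection to a plain covariate, and the fix takes account of it.

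What the objections do not remove is that the one covariate rule the article states depends on observed imbalance, and that the one word describing the estimand suggests change.

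**Conclusion.** The point holds in conditional form and should be acted on. As written, the analysis sentence points to a less efficient contrast for a primary outcome whose baseline value is already collected, and the stated covariate rule would not secure the better one. If the model is an unconstrained group-by-time or change contrast, 15 to 35% of its variance is avoidable for an assumed correlation of 0.7 to 0.3 (25% at 0.5), and the estimate is shifted by -(1 - rho)D given a chance baseline difference D. These sizes assume equal SDs and a single follow-up contrast; the power figures are for 108 per arm. If the full plan already conditions on baseline or constrains the baseline means, there is no loss and only the wording needs attention.

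**What to change.** Under Statistical analysis, Effectiveness, specify for each SF-36 subscale and for work ability one of the following:

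- **Preferred:** the longitudinal multilevel model with baseline as an outcome wave and the arm means constrained equal at baseline. This keeps patients whose baseline score is missing.
- **Alternative:** the 6, 12, 18 and 24-month scores as outcomes, with group, time, group-by-time, the baseline score on the same scale, and its interaction with time. The baseline term is always included, and missing baseline values are imputed.

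Under Effect evaluation, exempt this term from the imbalance rule. Replace *improvement* with the baseline-adjusted difference at follow-up, and report that. Work limitations share the same analysis sentence, but patients are sick-listed at entry, so whether a baseline score on that scale is meaningful should be settled before it is treated the same way.

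The cost is a few sentences, with no new data, visits or patients. The preferred form estimates one parameter fewer than the unconstrained model. The alternative uses one baseline slope per follow-up visit (four per model) and needs an imputation step.
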